### Choice Context and Hypothesis

The study aims to identify the key considerations that American Indian men make when deciding about whether to get screened for PC. The choice context presented to the participants in the DCE will be framed as follows:

*Your doctor informs you that there is a blood-based test for PC, and that you are eligible for this test due to your age. Please consider the following scenarios. In which of these scenarios would you be more likely to test for PC?*

We hypothesize that American Indian men evaluate several screening attributes, such as mortality benefit, unnecessary biopsies, and treatment, as well as contextual factors, such as experiences with PC and the manner in which information is presented, when considering PC screening [25].

DCE choice tasks will resemble the task shown in Table 2. The sample task includes attribute levels identified in the literature review and several attribute levels hypothesized a priori to influence the choices of American Indian men; the selection of attributes and attribute levels in the actual DCE will be guided by the findings from phase 2. Columns represent screening options. Rows describe the attributes identified in phase 2. Cells represent feasible levels for each attribute. Each choice task involves the comparison of 2 hypothetical PC screening tests, followed by an “opt-out” question, that is, whether the participant would get tested in the preferred scenario, which reflects a realistic choice based on current USPSTF PC screening recommendations [10]. This opt-out option provides a reference point that allows for estimates of the potential uptake of PC screening. Prior to the choice tasks, participants will be introduced to each attribute, presented with *ceteris paribus* conditions (eg, the participant has insurance that covers the test), and will complete a training and comprehension task.

**Table 2. T2:** Example of discrete choice experiment choice task.

Attribute	Option A	Option B	Option C
Chance of identifying PC^a^ after it has spread	100 out of 1000 men like you would have PC diagnosed after it has spread	200 out of 1000 men like you would have PC diagnosed after it has spread	N/A^b^

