Relative risk reduction of PC death from getting screened	Getting screened for PC would reduce the chance that you die because of PC by 25%	Getting screened for PC would reduce the chance that you die because of PC by 10%	Your chance of dying because of PC as a result of not getting screened is about 4%
Risk of false positive	4.6 men like you who get the test would have a biopsy from a false positive test result	2.3 men like you who get the test would have a biopsy from a false positive test result	N/A
Health care provider suggestion	Your doctor asks you whether you want to get screened	Your doctor suggests you get screened	Your doctor asks you whether you want to get screened
Which option do you prefer?	Option A	Option B	Option C

a PC: prostate cancer.

b Not applicable.

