### Outcome Measure

#### Primary and Secondary Outcomes

The main survey outcome of interest is the PC screening uptake, and the main analytic outcome is the association between each attribute level and the probability of PC screening uptake. The secondary outcome, which is the tradeoffs that American Indian men are willing to make when deciding about PC screening, will be described in the form of mRS. Results will be used to estimate participants’ relative preferences for all potential combinations of attribute levels, that is, PC screening. Feasible strategies can be ranked in terms of expected PC screening uptake, providing concrete guidance on the acceptability of alternative scenarios, and prioritizing specific strategies to increase PC screening uptake in Lumbee men.

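### Uptake is the main survey outcome, but the stated choice model leaves out the no-test answer, so any uptake figure would rest on a best-of-two share that tends to overstate uptake of one offered test

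*Protocol article*

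**What the plan says.** All references are to the protocol article.

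- **Choice Context and Hypothesis, stem.** The man is told that "there is a blood-based test for PC, and that you are eligible for this test due to your age". This is one test, to take or leave.
- **Same section, task.** "Each choice task involves the comparison of 2 hypothetical PC screening tests, followed by an" opt-out question: "whether the participant would get tested in the preferred scenario". Willingness to test in the scenario he rejected is not asked. On the purpose of the opt-out: "This opt-out option provides a reference point that allows for estimates of the potential uptake of PC screening".
- **Table 2.** The example task has another format: one question with columns A, B and C. C is no screening, as its mortality entry shows ("Your chance of dying because of PC as a result of not getting screened is about 4" per cent).
- **Primary and Secondary Outcomes.** "The main survey outcome of interest is the PC screening uptake". The main analytic outcome relates attribute levels to the probability of uptake, and "Feasible strategies can be ranked in terms of expected PC screening uptake".
- **DCE Data Analysis.** A mixed logit is fitted to a binary variable that is 1 for the option preferred in a task and 0 for its competitor, with effects-coded attribute levels as predictors. No opt-out alternative or constant is stated.

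**The concern.** Uptake of a single strategy means the probability that this strategy is taken when the alternative is no test. The task as described in the text observes something else: whether the better of two strategies is good enough to take. These two quantities differ, and the first can be had from such data only through a model that includes the no-test alternative. The model under DCE Data Analysis does not include it.

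An analyst who follows the text literally would have preference weights from the model and would have to take uptake from elsewhere. The two obvious sources are the raw proportion saying they would test, and a regression of that answer on the profile that won. The first tends to run high because it refers to a winner. The second runs high when the random error that made the profile win also drives the opt-out answer. The results are meant to show how acceptable different strategies are to Lumbee men, so an inflated level would give too favourable a picture of any single offer.

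**Working it through.** **Plan's own figures.** The protocol gives no uptake figure to reproduce. Its sample-size rule does reproduce (100 × 10 × 2 / 4 = 500) but does not bear on this point.

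**1. Why the stated model gives no uptake level.** Let a test with attributes x have utility c + xβ and let no test have utility 0, so that c sets the level of uptake. Then

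P(A preferred to B) = e^(c + x_Aβ) / [e^(c + x_Aβ) + e^(c + x_Bβ)] = 1 / [1 + e^(−(x_A − x_B)β)].

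The constant c cancels. β can be estimated and c cannot. Single-test uptake, e^(c + xβ) / [1 + e^(c + xβ)], needs c.

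**2. Size of a best-of-two share, equal attractiveness and shared errors.** Let p be single-test uptake (assumed, since the documents give none for Lumbee men) and o = p/(1 − p). With two equally attractive tests and the same random errors behind both answers, the share willing to test in the preferred scenario is 2o/(1 + 2o). For p = 50%, o = 1 and the share is 2/3.

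| Assumed single-test uptake | Best-of-two share | Excess (points) |
|---|---|---|
| 10% | 18.2% | 8.2 |
| 20% | 33.3% | 13.3 |
| 30% | 46.2% | 16.2 |
| 50% | 66.7% | 16.7 |
| 70% | 82.4% | 12.4 |
| 80% | 88.9% | 8.9 |
| 90% | 94.7% | 4.7 |

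**3. Relaxing those assumptions.** A random-utility simulation (400,000 draws per case) varied mean utility (−1.4, 0, 1.4), the spread of attractiveness between scenarios (SD 0 to 1 logit) and the spread between men (SD 0 to 2 logits).

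- Same errors behind both answers: excess of about 8 to 19 points (for example 70.2% became 78.5%, and 49.9% became 69.1%).
- Opt-out answer given as a fresh judgement with new error: excess of 0 to about 8 points (at most 49.9% became 57.7%), and zero when the two tests are equally attractive.

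**4. What different analyses of the same answers return.** One simulated design had three attributes, shared errors, no differences between men and a true mean single-test uptake of 50%:

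| Analysis | Uptake |
|---|---|
| Raw share willing to test | 69% |
| Logit on the chosen profile alone | 65% |
| Joint logit of A, B and no test | 50% |
| A against B only, as in DCE Data Analysis | weights recovered, no uptake level |

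**5. Table 2 format.** If the one-step A/B/C choice is fielded, the raw share choosing A or B is again a best-of-two share. The format therefore does not remove the problem, although it makes the joint model the natural analysis.

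**The case against.** A reader might infer that the task itself is biased, so that uptake is overstated whatever the analysis. The documents do not support this. Step 4 shows that a joint model of the same answers recovers single-test uptake under logit assumptions. The overstatement belongs to particular summaries of the data.

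A reader might also infer that the protocol defines uptake as the raw yes-share. It does not. It speaks of predicting the likelihood of uptake, of attribute effects on the probability of uptake, and of expected uptake per strategy, all of which point towards a modelled quantity. Nor does it propose a regression on the chosen profile. The Experimental Design section refers to a mixed multinomial logit, which could hold three alternatives. An article may fairly leave post-estimation formulas to a fuller plan. This stands, and it limits the point to the following: the dependent variable is stated, it covers two alternatives only, and it cannot deliver the uptake that the outcomes section promises.

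Three further limits stand. The claim that willingness is asked only for the preferred scenario rests on the text, and Table 2 shows another format. The size depends on assumptions the documents cannot settle; shares quoted in the literature review, such as the 4.6% choosing no screening in one French study, cannot be used as single-offer uptake, because the article does not say how many options lay behind them. Finally, no change in the ranking of strategies has been shown; the problem shown is in the level.

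**Conclusion.** The point holds in this form. Read together, the task description, the outcomes section and the analysis section do not produce the main survey outcome: the stated model gives attribute weights and no uptake level, and the substitutes at hand are best-of-two figures. In expectation the raw share does not fall below single-test uptake.

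The size is not in the documents. An assumed 50% shows as 67% under a logit with equally attractive tests and shared errors. If the opt-out answer is a fresh judgement, the excess is about 0 to 8 points, and selection on the first answer's error no longer inflates a chosen-profile regression.

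The same distinction matters for the remedy. Suppose the two-step question is fielded, the tests are equally attractive, and the second answer carries fresh error. A true 50% then shows as a 50% yes-share. A one-step three-way logit would read this as 2o/(1 + 2o) = 0.5, so o = 0.5 and p = 0.5/1.5 = 33%, which is too low. The likelihood must match the format actually fielded, so the text and Table 2 need to be reconciled first.

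**What to change.** 1. **Choice Context and Hypothesis / Table 2:** state which format will be fielded, the pair followed by an opt-out question or the single A/B/C choice.
2. **DCE Data Analysis:** model A, B and no test jointly, with an opt-out constant. If the two-step format is kept, say how the second answer enters the likelihood.
3. **Primary and Secondary Outcomes:** define uptake as the model-based probability that one stated strategy is chosen over no test, averaged over the estimated distribution of preferences.
4. **Reporting:** give any raw share only under a label such as *would test when offered a choice of two*.

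The cost is outcome wording, one added model term and a post-estimation step. The Results section says that no one has yet been recruited to the DCE, so on the article's account the change can still be made before data collection. Asking the would-test question for both A and B would be an alternative, at the price of one short extra question per task.

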### Outcome Measure

#### Primary and Secondary Outcomes

The main survey outcome of interest is the PC screening uptake, and the main analytic outcome is the association between each attribute level and the probability of PC screening uptake. The secondary outcome, which is the tradeoffs that American Indian men are willing to make when deciding about PC screening, will be described in the form of mRS. Results will be used to estimate participants’ relative preferences for all potential combinations of attribute levels, that is, PC screening. Feasible strategies can be ranked in terms of expected PC screening uptake, providing concrete guidance on the acceptability of alternative scenarios, and prioritizing specific strategies to increase PC screening uptake in Lumbee men.

#### Experimental Design and Choice Set Construction

Each respondent will be asked to complete 10 choice tasks. The attributes that will be tested include: (1) chance of dying from PC, (2) screening interval, (3) side effects of PC treatment, (4) risk of false positives, and (5) chance of finding harmful cancer. We will use 2 choice tasks designed to monitor attention and ensure participants understand the choice tasks; the first choice task will include a dominant choice and will be repeated halfway through the set of choice tasks. Robust statistical results can be obtained from a fractional factorial design of several dozen questions. Formally, we will use Ngene software (Sydney, Australia) to identify a *d*-efficient, partial factorial design that has good attribute-level balance to ensure that each respondent will see most or all attribute levels. To incorporate preference heterogeneity into the statistical design, the design will be optimized for mixed multinomial logit analysis, with simulations drawing priors from the estimated parameter distributions, which will be initially based on directional hypotheses and updated using relevant information from the phase 2 data. We will use a panel random parameter logit model to account for the inherent panel nature, with 500 Halton draws and normally distributed random parameters. Due to the anticipated small sample size, we will not implement blocking. We will use SurveyEngine survey software to design and host the final DCE. We will only include participants in the analyses if they answered all of the choice tasks.

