#### Sample Size and Statistical Power

Based on our past experience and DCE sample size recommendations, which combine the number of respondents (n), choice tasks (t=10), alternatives per task (a=2), and the maximum number of feature levels (c=4), and established a cutoff (nta/c≥500), we calculated that a sample size of 100 participants will provide sufficient power to characterize mean preferences for PC screening [39].

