#### DCE Data Analysis

We will analyze the choice data using mixed (random parameter) logit models [20]. The binary dependent variable will be 1 for the more preferred alternative and 0 for the other alternative in each choice task. The independent variables will be the effects-coded levels of each attribute. The mixed logit specification, estimated in STATA (StataCorp) version 16 or higher, allows for variation in preferences across respondents as well as error correlation across choice tasks within respondents. If we obtain more than 100 responses, we will also test latent class models to analyze the data, which may provide a better model fit. Latent class models will be estimated using Latent Gold Choice 5.0 software (Statistical Innovations).

The preference weights estimated using mixed logit models are the primary outcome of phase 3. Positive parameter estimates for effects-coded attribute levels indicate that an attribute level is more preferred compared to the mean, while negative parameter estimates indicate aversion. Tradeoffs will be described in the form of mRS.

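### A fixed 500 Halton draws may leave a simulation error of about 0.1 to 0.2 SE in a typical preference weight, and about half an SE in the worst one if preferences vary widely

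*Protocol article*

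**What the plan says.** The draw count stands in the Protocol article, section Experimental Design and Choice Set Construction: "We will use a panel random parameter logit model to account for the inherent panel nature", "with 500 Halton draws and normally distributed random parameters". The sentence follows the text on the Ngene design and precedes the decision not to block.

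The section DCE Data Analysis names the estimation software, "The mixed logit specification, estimated in STATA (StataCorp) version 16 or higher", and the coding: "The independent variables will be the effects-coded levels of each attribute". It gives no number or type of draws. It also makes the mixed logit preference weights the primary outcome of phase 3.

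The size of the model is only partly fixed. The design section lists five attributes, ending "and (5) chance of finding harmful cancer". The section Sample Size and Statistical Power uses "choice tasks (t=10), alternatives per task (a=2), and the maximum number of feature levels (c=4". The section Choice Context and Hypothesis keeps the final content open: "the selection of attributes and attribute levels in the actual DCE will be guided by the findings from phase 2".

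**The concern.** A mixed logit likelihood has no closed form. For each man, the probability of his ten choices is averaged over R draws from the assumed normal distribution of preferences, and the log of that average is maximised. With R too small for the number of random dimensions, the estimates depend on which draws were used. The model-based standard errors treat the simulated likelihood as exact, so they do not include this error, and a rerun with another draw set gives other weights.

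Marginal rates of substitution and predicted uptake are both built from these weights, so an unstable weight carries through to the trade-offs and the ranking of strategies. If the same setting also drives the design search, the D-error that it compares is noisy too.

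**Working it through.** **1. The plan's own figure.** With t = 10, a = 2, c = 4 and the cutoff nta/c ≥ 500, n = 500 × 4 / (10 × 2) = 100. The stated sample size is reproduced.

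**2. Number of random terms.** Effects coding gives L − 1 terms per attribute. Five attributes at four levels give 5 × 3 = 15, and at three levels 5 × 2 = 10. An opt-out constant adds one (16 or 11). Fifteen is a ceiling: four is a stated maximum, and no passage says which coefficients are random.

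**3. Quality of 500 plain Halton draws.** This is the largest correlation between two dimensions within one man's draws (burn-in 15, 100 men, normal transform), as the median over men.

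| Draws | 15 dimensions | 10 dimensions |
|---|---|---|
| 500 plain Halton | 0.18 (max 0.25) | 0.03 |
| 500 pseudo-random | 0.12 | 0.11 |
| 500 scrambled Sobol | 0.06 | not run |
| 2000 scrambled Sobol | 0.017 | not run |

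The defect appears near 15 dimensions and not at 10. Even at 15 it is the worst of 15 × 14 / 2 = 105 pairs; the median pair is about 0.01.

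**4. Effect on the weights.** Data were simulated for 100 men, one shared set of 10 tasks (the plan does not block) and the opt-out, then fitted by maximum simulated likelihood. The opt-out is needed because ten forced pairs give at most 10 independent contrasts, too few for 15 means. The articles' documents give no preference SD, effect sizes or final tasks, so these are assumptions. Shifts in the mean weights are in units of the model SE.

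Fits with 500 Halton draws against a 5000-draw Halton reference (3 to 4 datasets per setting, several draw sets each):

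| Random terms | Assumed SD | Median shift | 90th percentile | Share ≥ 0.5 SE | Worst weight per fit (median) |
|---|---|---|---|---|---|
| 16 | 0.5 | 0.09–0.10 | 0.24–0.29 | 1–3% | 0.31–0.34 |
| 16 | 1.0 | 0.24 | 0.56 | 15% | 0.61 |
| 11 | 0.5 | 0.07 | 0.18 | 0% | 0.22 |
| 11 | 1.0 | 0.24 | 0.57 | 16% | 0.65 |

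Fits of the same structure against a cleaner reference, 4096 scrambled Sobol draws: the typical weight moved about 0.1 to 0.2 SE. The worst weight per fit moved about 0.2 SE at SD 0.5 and 0.5 to 0.6 SE at SD 0.8.

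**5. What a shift means.** A 95% interval has a half-width of 1.96 SE. A shift of 0.5 SE is 0.5 / 1.96 = 26% of it, and a shift of 0.2 SE is 0.2 / 1.96 = 10%.

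**6. Does a larger count cure it?** In the fits against the Sobol reference, about 2000 scrambled Sobol draws cut the worst shift from 0.49 to 0.20 SE with 11 terms, but only from 0.63 to 0.44 SE with 16. In the fits against the Halton reference, 2000 draws changed the median shift with 16 terms from 0.10 to 0.06 SE at SD 0.5, and from 0.24 to 0.25 SE (no gain) at SD 1.0. With 11 terms at SD 1.0 it fell from 0.24 to 0.16 SE.

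**Limits.** There were few datasets per setting, tasks were random rather than D-efficient, both references carry noise of their own, and the attention-check tasks were not removed.

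**The case against.** The strongest reply has four parts.

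- **The sentence may concern the design only.** It sits in the design section, and the analysis section is silent on draws. This stands as an ambiguity. No other count is given, so a reader could carry 500 over to the estimation, but the article does not say so.
- **Fifteen random parameters are not planned.** This also stands. A reader might infer 15 from five attributes and c = 4, but four is the largest level count of any attribute and phase 2 settles the rest. The shifts do not vanish with fewer terms, however: at SD 1.0, 11 terms behave much like 16.
- **Halton correlation is not the cause.** This stands in part. The correlation is trivial at 10 dimensions, where large shifts still occur. In 12 further simulated datasets (15 random terms, SD 0.8, reference 4000 scrambled Sobol draws), 500 Sobol draws had a lower median worst shift than 500 Halton draws (0.38 against 0.58 SE) but a higher maximum (1.69 against 1.28 SE). Thin information, 100 men with 10 tasks each, contributes too.
- **A draw count is a software setting.** It can be changed after data collection, and a stability check is commonly left to an analysis plan. That makes the point modest. It does not remove it, because the article writes down a specific number.

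**Conclusion.** The point holds as a modest one about numerical precision. If 500 draws govern the estimation and about 10 to 15 coefficients are random, a typical weight carries a simulation error of about 0.1 to 0.2 SE (0.24 in the fits at SD 1.0). The most affected weight can move by about half an SE when heterogeneity is marked (assumed SD 0.8 or more). With moderate heterogeneity (SD 0.5) the worst shift is about 0.2 SE, or about 0.3 SE in the 16-term fits against the Halton reference. None of this appears in the reported standard errors.

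A reader might infer that the primary weights in general are off by half an SE or more. The check does not support that. Half an SE describes the worst weight in a fit under an assumed large SD, the protocol states no preference SD, and at SD 0.5 only 1 to 3% of weights reached that size with 16 terms and none with 11. Nor can 2000 draws be called sufficient in every case: with 16 terms and marked heterogeneity, a worst shift of 0.44 SE remained.

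**What to change.** 1. State which step the 500 draws govern: the Ngene design, the Stata estimation, or both.
2. For the primary estimation, replace the fixed count with scrambled quasi-random draws (Sobol or scrambled Halton). Start at about 2000 and double the number until no preference weight moves by more than about 0.2 SE. Report the final count and the largest remaining shift.
3. Say in advance what follows if the rule is not met at a practical count: reduce the number of random terms, or keep the model and report the remaining simulation error.

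Steps 1 and 2 cost only computing time and need no new data. Fewer random terms would restrict the heterogeneity that the model can describe, so that choice is best written down before fielding. The article's Results section reports that nobody has yet been recruited to the DCE.

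### One unblocked set of 10 paired tasks, analysed as A versus B only, does not secure identification of the primary preference weights

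*Protocol article*

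**What the plan says.** Under Experimental Design and Choice Set Construction the protocol article says "Each respondent will be asked to complete 10 choice tasks". It adds "We will use 2 choice tasks designed to monitor attention and ensure participants understand the choice tasks", and explains that "the first choice task will include a dominant choice and will be repeated halfway through the set of choice tasks". It does not say whether these two are among the 10 or additional. Five attributes are listed ("The attributes that will be tested include: (1) chance of dying from PC, (2) screening interval, (3) side effects of PC treatment", then false positives and finding harmful cancer), and the section on choice context leaves the final attributes and levels to phase 2. The same design section says "Robust statistical results can be obtained from a fractional factorial design of several dozen questions" and later "Due to the anticipated small sample size, we will not implement blocking".

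Sample Size and Statistical Power uses 10 tasks, 2 alternatives and "the maximum number of feature levels (c=4" to reach 100 men. DCE Data Analysis defines a binary outcome, preferred alternative against the other, and states "The independent variables will be the effects-coded levels of each attribute". The preference weights from that model are the primary outcome of phase 3. Choice Context and Hypothesis says an opt-out question follows each pair, but the dependent variable does not mention it.

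**The concern.** In a paired-choice model each distinct task supplies one row of attribute differences. If all men see the same tasks, those rows are all there is. A larger sample repeats them and makes their choice shares more precise, but adds no new direction. If there are fewer rows than coefficients, some combinations of level weights cannot be estimated. Random parameters do not recover the means along those directions.

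The marginal rates of substitution are ratios of these weights, and the ranking of screening strategies by expected uptake is built from them, so both would fail along with the primary outcome.

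The reason given for not blocking does not hold. With 100 men and 10 tasks there are 1,000 responses with or without blocks. Blocking only spreads them over more distinct comparisons. The design section also describes a design of several dozen questions, which 10 common tasks do not supply.

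**Working it through.** **1. The plan's own figure.** The rule is n × t × a / c ≥ 500. With n = 100, t = 10, a = 2, c = 4: 100 × 10 × 2 / 4 = 500, so n = 100 reproduces. The rule counts responses. It would give 500 whether the men saw 10 distinct tasks or 40, so it cannot detect an identification problem.

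**2. Distinct comparisons (T).** The repeat of the dominant task adds no row.
- Checks inside the 10, both set aside: T = 10 − 2 = 8.
- Checks inside the 10, dominant task kept once: T = 10 − 1 = 9.
- Checks additional to the 10: T = 10.

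**3. Coefficients needed (K).** Effects coding needs (levels − 1) per attribute. Only the maximum, 4, is stated. I assume 2 to 4 levels each, with at least one attribute at 4.

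| Levels | K | T = 8 | T = 9 | T = 10 |
|---|---|---|---|---|
| 4,2,2,2,2 | 3+1+1+1+1 = 7 | yes | yes | yes |
| 4,3,2,2,2 | 8 | yes | yes | yes |
| 4,3,3,2,2 | 9 | no | yes | yes |
| 4,3,3,3,2 | 10 | no | no | yes |
| 4,3,3,3,3 | 3+2+2+2+2 = 11 | no | no | no |
| 4,4,3,3,3 | 12 | no | no | no |
| 4,4,4,4,4 | 5 × 3 = 15 | no | no | no |

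The entries say whether the A-minus-B matrix can have rank K, taking the best of 1,500 random designs for each case. The rank cannot exceed T, so each "no" follows from counting alone.

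**4. How much of the level space fails.** Under the assumption in step 3 there are 3⁵ − 2⁵ = 243 − 32 = 211 level assignments. K exceeds T in 186 of them at T = 8 (88%), 146 at T = 9 (69%) and 96 at T = 10 (45%). These are counts of combinations, not probabilities.

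**5. Which assignments are realistic.** Table 1 lists 7 + 6 + 5 + 6 + 4 = 28 attributes over five studies. Two have two levels (screening technique and mortality reduction, both in one French study) and 26 have three or more. K ≤ 8 requires at least three of the five attributes to have two levels, and K ≤ 10 requires at least one.

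**6. With the opt-out modelled.** Each task then gives up to 2 contrasts, and the model needs K + 1 parameters (8 to 16).
- T = 8: up to 16 contrasts, so 16 − 16 = 0 to 16 − 8 = 8 spare. K = 11 leaves 16 − 12 = 4.
- T = 10: up to 20 contrasts, so 4 to 12 spare.

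Full rank was reached in every case in the table.

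**7. With more distinct tasks.** Using A/B data alone, 24, 30, 32 and 40 distinct tasks each reached full rank for K = 7, 11 and 15.

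**The case against.** A reader might infer that the main effects are not identified under this plan, whatever the sample size. The documents do not support that. Levels per attribute are not fixed, and K of 7 or 8 is estimable on 8 tasks, as is K up to 10 on 10. The count of 8 is itself an assumption, because the check tasks may be additional. A single common set is the natural reading of no blocking, but random draws from a larger design are not expressly excluded. Nor does the protocol say that several dozen questions are required; it says that such a design can give robust results.

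The opt-out matters most. It is collected after every pair, Table 2 shows it as a third option, and the main analytic outcome, the probability of uptake, cannot be obtained without it. If it enters the model, identification can be restored even on 8 tasks. All of this stands and makes the concern conditional. But the stated dependent variable leaves the opt-out out.

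It is also fair to say that a d-efficient search would expose a design with fewer contrasts than parameters, since its information matrix is singular, and fielding has not begun. Silent failure is therefore unlikely. However, the search helps only if it is run for the model that will be fitted, and the no-blocking sentence rules out the obvious remedy. Limiting the number of levels would also work, but it narrows what the study can describe.

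**Conclusion.** The concern holds in conditional form. The design, sample size and analysis sections together do not secure identification of the primary preference weights: 8 to 10 distinct A/B comparisons stand against 7 to 15 coefficients. If every attribute has at least 3 levels and one has 4, the pattern that Table 1 points to, K is at least 11 and the A/B model fails at any sample size, even with 10 informative tasks. If most attributes have two levels, it is estimable. Modelling the opt-out can rescue it, with 0 to 4 spare contrasts for K of 11 to 15 on 8 tasks.

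This rests on five attributes, 2 to 4 levels each with at least one at 4, main effects only, one task set common to all men, and the dependent variable as written. The faulty rationale for not blocking does not depend on the level counts.

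**What to change.** - Remove the no-blocking sentence. Generate about 24 to 40 distinct tasks (for example 3 × 8 = 24 or 4 × 10 = 40), divide them into 3 or 4 level-balanced blocks, and randomise each man to one block.
- State the levels of each attribute once phase 2 is complete, and whether the two check tasks are inside or outside the 10.
- Include the opt-out response in the model under DCE Data Analysis, and optimise the design for that same model.
- Before launch, confirm full column rank for the final level list with the check tasks excluded.

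No extra men or tasks per man are needed, only a blocking option in the design software and a block allocator in the survey platform. The downside is fewer responses to each individual task: 100/4 = 25 to 100/3 ≈ 33 men per block, instead of 100. The change must come before fielding. Once one fixed set has been used, neither more men nor a different analysis of the A/B data repairs a rank deficiency.
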